## Abstract

**Background:**

Postoperative atrial fibrillation (POAF) is a common complication following cardiac surgery. POAF is associated with increased morbidity and hospital costs. We herein describe the protocol for a randomized controlled trial to determine if performing a posterior left pericardiotomy prevents POAF after cardiac surgery.

**Methods/design:**

All patients submitted to cardiac surgery at our institution will be screened for inclusion into the study. The study will consist of two parallel arms with random allocation between groups to either receive a posterior left pericardiotomy or serve as a control. Masking will be done in a single-blinded fashion to the patient. Patients will be continuously monitored postoperatively for the occurrence of atrial fibrillation until discharge. At the follow-up clinic visit (15–30 days after surgery), the primary endpoint (atrial fibrillation) and other secondary endpoints, such as pleural or pericardial effusion, will be assessed. A total sample size of 350 subjects will be recruited.

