#### Outcomes

The primary outcome of the study is the occurrence of POAF, defined as the occurrence of an irregularly irregular heart rhythm, without detectable P waves, lasting more than 30 s observed during the hospital stay. Patients will be monitored continuously during the entire hospital stay with the Philips Intellivue MP70 patient monitor (Philips, Andover, MA, USA) and alarm strips will be collected for analysis and POAF adjudication. A standard 12-lead electrocardiogram (EKG) will be recorded on a daily basis and collected for analysis and POAF adjudication. Additional 12-lead standard EKGs ordered at the discretion of the caring physician will be collected for analysis and POAF adjudication. An independent committee blinded to group assignment will adjudicate episodes of POAF. The secondary outcome measures of the study will include: (1) time spent in atrial fibrillation, defined as the time from the first evidence of atrial fibrillation to the first evidence of sinus rhythm restoration on cardiac monitoring strips or standard EKG, (2) duration of hospitalization, (3) antiarrhythmic drug use, and (4) need for electrical cardioversion. Safety outcomes will be (1) incidence of left pleural effusion, (2) incidence of pericardial effusion, (3) MAE, and (4) death.

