#### Participant timeline

The main outcome of interest is the occurrence of POAF after cardiac surgery. Patients will first be screened for eligibility and willingness to participate in the trial. Then, informed consent will be collected from participating patients, who will be randomized into one of the two study groups. Postoperatively, patients will be closely monitored for the occurrence of atrial fibrillation, pleural and pericardial effusions. Times of event and to discharge will also be assessed. These outcomes will be monitored until the time of the follow-up visit, which will be within 30 days postoperatively for the majority of patients at our institution. Participation until this time point represents complete participation in the trial. We intend to include only patients who have completed follow-up (Fig. 2).

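### The primary endpoint window is stated inconsistently: the formal definition ends at discharge, while two other statements carry atrial fibrillation to the follow-up visit

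*Protocol article*

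**What the plan says.** **Formal definition.** Protocol article, Outcomes (under participants, interventions, outcomes) defines the primary outcome as an irregularly irregular rhythm without detectable P waves, "lasting more than 30 s observed during the hospital stay". The same paragraph gives the means of detection: "Patients will be monitored continuously during the entire hospital stay with the Philips Intellivue MP70 patient monitor", plus a daily 12-lead EKG and any further EKGs that the treating physician orders. An independent committee, blinded to group, adjudicates episodes. The paragraph appears again, in practically the same words, in the Outcomes subsection of Data management.

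**Abstract, Methods/design.** One sentence agrees with the definition: "Patients will be continuously monitored postoperatively for the occurrence of atrial fibrillation until discharge". The next does not: "At the follow-up clinic visit (15–30 days after surgery), the primary endpoint (atrial fibrillation) and other secondary endpoints" will be assessed.

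**Participant timeline.** After surgery, "patients will be closely monitored for the occurrence of atrial fibrillation, pleural and pericardial effusions". Times of event and to discharge are added, and then: "These outcomes will be monitored until the time of the follow-up visit, which will be within 30 days postoperatively" for most patients. The section ends with: "We intend to include only patients who have completed follow-up".

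**Analysis.** Additional analyses tests the primary outcome by intention to treat, with all participants in their assigned groups. Sample size allows for 10% loss to follow-up or dropout.

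**The concern.** The primary endpoint needs one start, one end and one method of detection. Here the end is discharge in the formal definition and the clinic visit in the two other statements. The difference decides whether some patients count as events.

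Three things are at stake:

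- **Detection changes at discharge.** A threshold of more than 30 s makes sense under continuous monitoring. The text describes nothing comparable afterwards, so a longer window would add episodes found by another, unstated route.
- **Completeness.** Under the hospital window the primary outcome is known when the patient leaves. Under the longer window it is complete only for patients who reach the visit.
- **Choice of event set.** While both windows stand in the document, either count can be presented as the planned one after the results are known. The interim stopping rule also acts on the incidence of the primary outcome, so it needs the same single definition.

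**Working it through.** **Step 1. The statements side by side.**

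| Place | End of the AF window |
|---|---|
| Outcomes | Hospital stay |
| Outcomes, under Data management | Hospital stay |
| Abstract, sentence on continuous monitoring | Discharge |
| Abstract, sentence on the clinic visit | Visit, 15–30 days after surgery |
| Participant timeline | Follow-up visit, within 30 days for most patients |

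**Step 2. One patient.** A patient has no AF in hospital, goes home, and has a first AF recorded on day 20. Under the definition this is a non-event. Under the abstract's clinic-visit sentence and Participant timeline it is an event. No calculation is needed to show the conflict.

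**Step 3. Does the sample size depend on the answer?** The plan's figures reproduce with alpha 0.05, two-sided (the sides are assumed):

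- 30% vs 15%, 90% power, pooled variance: n per arm = [1.960·√(2·0.225·0.775) + 1.282·√(0.30·0.70 + 0.15·0.85)]² / 0.15² = 160.8, rounded up to 161. The total is 322, as stated.
- 40% vs 20%, 80% power, unpooled variance: n per arm = (0.24 + 0.16)·(1.960 + 0.842)² / 0.20² = 78.5, rounded up to 79. The total is 158, as stated.

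Fixing the window as the hospital stay changes neither figure.

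**Step 4. How much could the longer window matter?** The documents give no rate of AF after discharge, so this step is an illustration only. Assume that a fraction q of patients AF-free at discharge is recorded with AF by the visit, and that q is the same in both arms. Each rate p becomes p + (1 − p)·q, so the difference between arms shrinks by the factor (1 − q). The number reclassified, starting from 30% vs 15%, is 175·(0.70 + 0.85)·q. Power is for 175 per arm with no dropout, by the pooled formula.

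| q (assumed) | Rates | Reclassified of 350 | Power | Total for 90% power |
|---|---|---|---|---|
| 0 | 30.0% vs 15.0% | 0 | 0.92 | 322 |
| 2% | 31.4% vs 16.7% | 5.4 | 0.90 | 352 |
| 5% | 33.5% vs 19.25% | 13.6 | 0.86 | 398 |
| 10% | 37.0% vs 23.5% | 27.1 | 0.79 | 484 |

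For scale, 30% vs 15% gives 175·0.30 + 175·0.15 = 78.75 expected events. Starting from 40% vs 20%, power falls only from 0.985 to 0.94 over the same range of q. If the intervention also reduced AF after discharge, the dilution would be smaller than shown.

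**Step 5. The completed-follow-up sentence.** It would exclude a patient who was fully monitored in hospital and then missed the visit. Intention to treat, as described in Additional analyses, would keep that patient. Under the hospital window the primary outcome is already known, so the exclusion has no purpose for it.

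**The case against.** **The definition governs.** It is given twice, once among the statistical methods, with a rhythm criterion, a duration threshold, a named monitor and adjudication. Against it stand one abstract sentence and one narrative paragraph. In the abstract, assessment at the visit could mean that in-hospital status is compiled at the last contact. In Participant timeline the list also includes time to discharge, which cannot be followed to a later visit, so the phrase is loose. Most of this stands: a reader might infer two rival primary endpoints, and the documents do not support that. What does not stand is that the conflict disappears, because Participant timeline names AF itself and carries it to the visit.

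**Detection after discharge.** A reader might infer that later AF would be found only by chance or symptoms and classified by unblinded staff. The documents do not establish this. The schedule and timeline figures are not shown and may include a rhythm check at the visit, and a blinded committee adjudicates episodes. Two narrower points remain. The text describes no recording after discharge comparable to continuous monitoring, and the committee can judge only the recordings that reach it.

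**Attendance.** A reader might blame the longer window for making the primary outcome depend on clinic attendance. The completed-follow-up sentence has that effect under either window, so aligning the window alone does not cure it.

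**Size.** Any rate of AF after discharge is an assumption. In the illustration, power stays at 0.86 or above for q up to 5%. A claim that the trial would be underpowered is not supported.

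**Conclusion.** The point holds as an inconsistency in the stated window of the primary endpoint. The hospital-stay definition dominates and matches the monitoring described. The abstract's clinic-visit sentence and Participant timeline contradict it, and a first AF between discharge and the visit changes status accordingly.

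The number of patients affected cannot be taken from the documents and may be small. The 5 to 27 of 350 shown above rests wholly on the assumed q of 2% to 10%, equal in both arms, and on the 30% vs 15% scenario. The stronger reason to correct the text is that the primary event count should not be open to two readings. Neither the planned 350 nor the figures behind it are in question here.

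**What to change.** 1. State one window everywhere: adjudicated postoperative AF from end of surgery to discharge, following both Outcomes paragraphs.
2. In the abstract, remove the primary endpoint from the clinic-visit sentence and leave the other endpoints there.
3. In Participant timeline, exclude the primary AF endpoint from the outcomes followed to the visit.
4. In the same section, state that the completed-follow-up restriction does not apply to the primary intention-to-treat analysis, because that outcome is known at discharge.

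AF found after discharge may be reported descriptively, outside the primary endpoint. A new formal secondary outcome is not needed, and would require its own method of detection.

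The cost is wording in two sections. No extra data, patients or sample size calculation are required. The change should be made before any comparison of the primary outcome by group is seen.

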**Discussion:**

POAF is associated with increased morbidity, prolonged hospital stay, and increased costs after cardiac surgery. Several strategies aimed at reducing the incidence of POAF have been investigated, including beta-blockers, amiodarone, and statins, all with suboptimal results. Posterior left pericardiotomy has been associated with a reduction of POAF in previous series. However, these studies had limited sample sizes and suboptimal methodology, so that the efficacy of posterior pericardiotomy in preventing POAF remains to be definitively proven. Our randomized trial aims to determine the effect of a posterior left pericardiotomy on the incidence of POAF.

**Trial registration:**

ClinicalTrials.gov, ID: NCT02875405, protocol record 1502015867. Registered on July 2016.

**Electronic supplementary material:**

The online version of this article (doi:10.1186/s13063-017-2334-4) contains supplementary material, which is available to authorized users.

## Background

Postoperative atrial fibrillation (POAF) is a common complication following cardiac surgery with an incidence of 30–40% [1, 2]. POAF has been associated with stroke, systemic embolism, and cardiac failure. Its detection mandates additional treatment with varying combinations of drugs to control cardiac rate and/or rhythm, anticoagulation, and/or electrical cardioversion; each of which have side effects that cannot be ignored. As a result, POAF prolongs hospital stay and increases hospital expenditure [1]. Several strategies aimed at reducing the incidence of POAF have been investigated, including treatment with beta-blockers, amiodarone, and statins, all with unsatisfactory results [1, 3–5]. In a few studies, performing a posterior left pericardiotomy has been associated with a reduction in the incidence of POAF by allowing drainage of blood and fluid from the posterior pericardial space [6–8]. Performing a posterior left pericardiotomy is theorized to prevent POAF by allowing the posterior pericardial space to drain into the left side of the chest and be evacuated by a chest tube. This prevents blood and fluid from accumulating behind the left atrium, causing atrial irritation which can lead to POAF. However, previous studies are associated with some limitations such as: sample size, inclusion/exclusion criteria, randomization procedure, and suboptimal electrocardiographic monitoring strategies. Moreover, posterior left pericardiotomy requires additional operative time and can be associated with procedure-specific complications such as an increased incidence of left-sided pleural effusion. As a result, current evidence on posterior pericardiotomy has failed to translate into changes to clinical practice.

The primary objective of the present prospective, randomized, controlled study is to assess whether performing a posterior left pericardiotomy during open cardiac surgery procedures (coronary artery bypass grafting (CABG), aortic valve replacement, interventions to the ascending aorta or their combination) results in a reduction in the incidence of POAF.

The secondary objectives of this study are to assess:The time spent in atrial fibrillationThe duration of the hospitalizationSafety measures such as: pericardial and left-sided pleural effusion as a complication of this procedure, death, and major adverse events (MAE)

This study contributes to the cardiovascular community’s understanding of POAF and has the potential to offer an alternative treatment option that mitigates the need for anticoagulation and antiarrhythmic drugs along with their associated side effects. This is especially important for patients who have contraindications to either anticoagulation or antiarrhythmic therapy.

## Methods and design

The study was designed according to the Recommendations for Interventional Trials (SPIRIT) guidelines (see Additional file 1: SPIRIT Checklist, Figure S1).

### Methods: participants, interventions, outcomes

#### Study setting

The Department of Cardiothoracic Surgery at Weill Cornell Medicine/New York Presbyterian Hospital.

#### Eligibility criteria

Included subjects will be patients undergoing open cardiac surgery for interventions on the coronary arteries, the aortic valve, and/or the ascending aorta who have no previous history of atrial fibrillation. Exclusion criteria are as follows: pre-operative non-sinus rhythm, history of previous atrial arrhythmia of any type, reoperation, mitral or tricuspid valve disease, surgery of the descending thoracic or thoraco-abdominal aorta, need for hypothermic circulatory arrest, off-pump operations, urgent or emergent presentation, disease of the left-sided pleura or previous left-sided instrumentation, non-cardiac-related comorbid contraindications to surgery, and chest deformity of any kind.

#### Interventions

In the intervention group, a posterior left pericardiotomy will be performed according to technique described in the surgical literature [9]. In brief, if not already entered, the left pleural space will be entered through the pre-existing median sternotomy. A 4-cm incision will be made posterior to the phrenic nerve in a parallel and longitudinal fashion extending from the left inferior pulmonary vein to the diaphragm. We will use the tip of the mediastinal tube that is placed in all cardiac surgery patients (instead of an additional chest tube) for drainage of the left-sided pleura so that patients of the treatment group will not have a higher level of postoperative pain or discomfort. The estimated additional surgery time is 15 min.

#### Concomitant care

According to our current practice, patients who were taking beta-blockers pre-operatively will continue taking the beta-blocker up to the time of surgery. After surgery, all patients are given beta-blockers per os starting on postoperative day 1, except those who are bradycardic (heart rate < 65 beats per minute (bpm)), require epicardial pacing, have AV block, or are receiving beta agonists, such as epinephrine or dobutamine. In those cases, when the patient’s intrinsic heart rate increases to > 65 bpm, AV block resolves, or epinephrine is discontinued, beta-blockers are then initiated. Any inotropic agents that may contribute to development of atrial arrhythmias are weaned and discontinued as rapidly as the patients’ hemodynamic parameters will allow. This protocol will be applied in both groups in the same way. All patients will have an immediate postoperative chest radiograph (CXR) followed by a daily morning CXR for the entire hospitalization. Patients who are discharged with a moderate or larger pleural effusion will have another CXR when they are evaluated in clinic 2–3 weeks after discharge. A transthoracic echocardiogram will be performed before discharge and at the follow-up visit, to evaluate for pericardial effusion (SPIRIT Figure, Fig. 1). In case of evidence of moderate-to-severe pericardial effusion, further echocardiography or computer tomography evaluation and drainage will be performed when necessary.

**Fig. 1 Fig1:**
[figure not shown]
Standard Protocol Items: Recommendations for Interventional Trials (SPIRIT) Figure

#### Outcomes

The primary outcome of the study is the occurrence of POAF, defined as the occurrence of an irregularly irregular heart rhythm, without detectable P waves, lasting more than 30 s observed during the hospital stay. Patients will be monitored continuously during the entire hospital stay with the Philips Intellivue MP70 patient monitor (Philips, Andover, MA, USA) and alarm strips will be collected for analysis and POAF adjudication. A standard 12-lead electrocardiogram (EKG) will be recorded on a daily basis and collected for analysis and POAF adjudication. Additional 12-lead standard EKGs ordered at the discretion of the caring physician will be collected for analysis and POAF adjudication. An independent committee blinded to group assignment will adjudicate episodes of POAF. The secondary outcome measures of the study will include: (1) time spent in atrial fibrillation, defined as the time from the first evidence of atrial fibrillation to the first evidence of sinus rhythm restoration on cardiac monitoring strips or standard EKG, (2) duration of hospitalization, (3) antiarrhythmic drug use, and (4) need for electrical cardioversion. Safety outcomes will be (1) incidence of left pleural effusion, (2) incidence of pericardial effusion, (3) MAE, and (4) death.

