##### Outcomes

The primary outcome of the study is the occurrence of POAF, defined as the occurrence of an irregularly irregular heart rhythm, without detectable P waves, lasting more than 30 s observed during the hospital stay. Patients will be monitored continuously during the entire hospital stay with the Philips Intellivue MP70 patient monitor (Philips, Andover, MA, USA) and alarm strips will be collected for analysis and POAF adjudication. A standard 12-lead electrocardiogram (EKG) will be recorded on a daily basis and collected for analysis and POAF adjudication. Additional 12-lead standard EKGs ordered at the discretion of the caring physician will be collected for analysis and POAF adjudication. An independent committee blinded to group assignment will adjudicate episodes of POAF. The secondary outcome measures of the study will include: (1) time spent in atrial fibrillation, defined as the time from the first evidence of atrial fibrillation to the first evidence of sinus rhythm restoration on cardiac monitoring strips or standard EKG, (2) duration of hospitalization, (3) antiarrhythmic drug use, (4) need for electrical cardioversion. Safety outcomes will be (1) incidence of left-sided pleural effusion, (2) incidence of pericardial effusion, (3) MAE, and (4) death.

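### The outcome called time spent in atrial fibrillation stops at the first return to sinus rhythm, so it measures only the first episode and leaves out recurrences

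*Protocol article*

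**What the plan says.** The Background section of the protocol article names time spent in AF as a secondary objective, with no limit to one episode.

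The Outcomes section under Methods: participants, interventions, outcomes makes it item (1) of the secondary outcomes and gives the operational rule: "time spent in atrial fibrillation, defined as the time from the first evidence of atrial fibrillation to the first evidence of sinus rhythm restoration". The Outcomes section under Data management repeats it: "the time from the first evidence of atrial fibrillation to the first evidence of sinus rhythm restoration on cardiac monitoring strips or standard EKG".

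The same sections describe how rhythm is observed: "Patients will be monitored continuously during the entire hospital stay". Alarm strips, a daily 12-lead EKG and any further EKGs ordered by the treating physician are collected. On review of these, "An independent committee blinded to group assignment will adjudicate episodes of POAF".

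Under Additional analyses, secondary outcomes are to be analysed by descriptive statistics. Statistical methods adds univariate comparison of postoperative differences between the groups.

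**The concern.** The name of the outcome and its definition describe different quantities. Time spent in AF is a total over the stay. An interval from a first onset to a first conversion is the length of one episode. The two agree only in patients who have a single episode.

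Two consequences follow if the rule is applied as written. First, the reported AF time is too low for every patient who relapses. Second, the comparison between groups cannot register any difference in recurrence. It could also show an apparent gain if one long episode in one group corresponded to several shorter ones in the other.

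This is separate from the question of patients who never convert. Here the clock stops at a genuine conversion, and the later AF is then lost.

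**Working it through.** The plan states no figure for this outcome, so there is nothing to reproduce. The check has three parts: reading the passages together, a worked example, and an illustrative range.

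**1. The passages side by side**

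| Place in the protocol article | Content | Bearing on recurrences |
|---|---|---|
| Background, secondary objectives | Time spent in AF | No limit to one episode |
| Outcomes (Methods) | First evidence of AF to first evidence of sinus rhythm | One interval per patient |
| Outcomes (Data management) | Same definition | One interval per patient |
| Outcomes (both) | Continuous monitoring; episodes adjudicated | Recurrences can be seen |
| Participant timeline | Times of event and to discharge assessed | Does not alter the definition |
| Additional analyses | Secondary outcomes described | Does not alter the definition |

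No section says that the clock restarts at a recurrence or that episodes are added.

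**2. What the rule scores (assumed durations)**

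| Patient | AF episodes | Score as written | Total time in AF |
|---|---|---|---|
| A | 2 h, 10 h, 12 h | 2 h | 2 + 10 + 12 = 24 h |
| B | 24 h | 24 h | 24 h |
| C | 0.5 h, then 48 h | 0.5 h | 0.5 + 48 = 48.5 h |
| D | 6 h | 6 h | 6 h |

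A and B spent the same time in AF but score 2 h and 24 h. C spent about eight times as long in AF as D (48.5 / 6 = 8.1) but scores lower, so the order is reversed.

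**3. Share of AF time captured**

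Let N be the number of patients with AF, m the mean episode length, and r the share of them with exactly one recurrence of the same mean length.

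- Time counted by the rule: N × m
- Total time in AF: N × m + r × N × m = N × m × (1 + r)
- Share captured: 1 / (1 + r)

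| r (assumed) | Share captured |
|---|---|
| 0.1 | 1 / 1.1 = 91% |
| 0.3 | 1 / 1.3 = 77% |
| 0.5 | 1 / 1.5 = 67% |

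The answer depends on the model as well as on r. If instead every episode is followed by another with probability r, the mean number of episodes is 1/(1 − r) and the share captured is 1 − r: 90%, 70% and 50% at the same three values.

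**4. Effect on the comparison between groups**

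Under the one-recurrence model, the ratio of mean AF time per AF patient (intervention over control) is [m_T × (1 + r_T)] / [m_C × (1 + r_C)]. The rule as written gives m_T / m_C. If r is the same in both groups, the ratio is preserved and only the absolute times are too low. If r differs, the ratio is wrong by the factor (1 + r_T) / (1 + r_C). The article gives no value for either r.

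**The case against.** **The wording may be a rule for timing one episode.** First evidence can be read as detection language: the earliest tracing that shows AF, then the earliest that shows conversion. Episodes are adjudicated in the plural, and a full protocol or analysis plan that is not shown might say how to combine them. This reading is conceivable but written nowhere. The article does not leave the matter open: it gives a complete rule for the outcome, twice, and that rule yields one interval per patient. If a sum was intended, the sentence still has to say so, or those who extract the data may record different values.

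**The consequences are limited.** This stands. The primary outcome is the occurrence of any qualifying episode in hospital and does not use this definition. The secondary outcomes are mainly descriptive. Being item (1) is only list order, since no hierarchy is stated. Antiarrhythmic drug use, cardioversion and length of stay may partly reflect recurrent AF, although none of them measures time in AF.

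**Timing later episodes may be harder than it looks.** This also stands in part. The article says that alarm strips and EKGs are collected. It does not say that full continuous recordings are kept.

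**A stronger reading that the documents do not support.** A reader might infer that the rule costs the trial substantial power, or hides a real effect of the procedure on recurrence. Any power figure would have to rest on assumed recurrence rates in each group. If first episodes are assumed alike in both groups, the first-episode comparison has power equal to alpha by construction, which says nothing about the rule itself. The mechanism in the Background section concerns fluid leading to the onset of AF. An effect on recurrence is an inference from it.

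**Conclusion.** The point holds as a defect of definition. As written, the outcome is the duration of the first AF episode, not time spent in AF. It is too low for any patient with recurrent AF and can put patients in the wrong order. That conclusion needs no assumption about recurrence rates beyond some patients relapsing before discharge.

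The size of the loss cannot be derived from the article. The range of 91% to 67% captured, for r from 0.1 to 0.5, is an illustration that assumes at most one recurrence, of equal mean length. No claim about power is made. The primary outcome and the sample size do not change. The correction should be made, because the outcome will otherwise be reported under a name that it does not fit.

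**What to change.** In both Outcomes sections, define the outcome as the sum of the durations of all adjudicated AF episodes from end of surgery to discharge. Time each episode from the first evidence of AF to the first evidence of sinus rhythm on the strips and EKGs already collected. Keep first-episode duration as a descriptive item.

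Before adopting this, check that the retained strips allow onset and conversion of later episodes to be timed reliably. If they do not, rename the outcome as duration of the first AF episode and adjust the secondary objective in the Background section to match.

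The cost is one sentence in each of the two sections, a repeated-episode field on the data form, and timing more than one episode in some patients.
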